#### EEG Recording

1.2.2

QEEG is software that quantitatively extracts EEG data for numerical analysis. QEEG parameters: The scalp records the electrical potentials associated with the brain, known as EEG. The four rhythms of delta, theta, alpha, and beta are considered the main frequency bands of brain waves. Delta rhythm covers the frequency range from 1 to 4.0 Hz, theta (4–8 Hz), alpha (8–12 Hz), broad beta (12–25 Hz), and hi‐beta (25–30 Hz). All frequency rhythms take into account the following parameters: absolute power, relative power, power ratio, peak frequency, amplitude asymmetry, coherence, and phase lag.
✓Absolute power: The amount of wave energy in a specific frequency spectrum in the frequency domain.✓Relative power: Divide the absolute power of a specific frequency band by the total absolute power of all frequency bands.✓Power ratio: Divide the power of one frequency band by the power of another frequency band.✓Peak frequency: The peak detection method for computerized EEG analysis involves measuring the amplitude and time interval between successive maxima (peaks) and minima (crossings) in a signal.✓Amplitude asymmetry: There are neuroanatomical differences between the left and right sides of the brain, as well as lateral functional differences, also known as lateralization of brain function. Asymmetry is usually calculated by subtracting the natural logarithm of the left hemisphere‐specific frequency power from the right hemisphere‐specific frequency power natural logarithm while using link ears as the reference electrode.

There are neuroanatomical differences between the left and right sides of the brain, as well as lateral functional differences, also known as lateralization of brain function. Asymmetry is usually calculated by subtracting the natural logarithm of the left hemisphere‐specific frequency power from the right hemisphere‐specific frequency power natural logarithm while using linked ears as the reference electrode.
✓Coherence: Coherence represents the correlation coefficient between two signals, which can be a measure of the phase stability between two signals at a certain frequency and can take a value between 0 and 1. A coherence of zero indicates very large phase changes between two signals, while a Coherence of 1 indicates that the two signals have a constant phase difference over time.✓Phase lag: A method for estimating connectivity in EEG in a way that excludes volume conduction effects. The phase difference for a sinusoidal waveform is the amount of angular displacement of the waveform relative to a given reference point on the horizontal axis. This angle is measured in degrees or radians. In other words, the phase difference between two waves is the difference between two waveforms relative to a common axis.

To obtain these parameters, first, the assembly of all the recorded data is defined based on the linked‐ear assembly. Then, Neuro‐Guide software is used to convert brain waves into quantitative data.

In this study, all EEG recordings will be done between 2:00 p.m. and 4:00 p.m. Persons with mild cognitive impairment will be invited for an EEG recording the day after the cognitive examination. The day before the EEG recording, the subjects wash their heads in a bath to remove all residues from the scalp. We advise the instructed person not to change their usual daily routine before the EEG recording and to continue taking their main medication. After arriving at the EEG recording site, we give the subject time to rest and adapt to the environment. To avoid increased impedance due to sweating and soiling, the scalp will be cleaned once more using an alcohol pad, and all devices such as cell phones will preferably be kept away from the room because they produce disturbing noises. The room will be kept quiet certainly during EEG recording, and the EEG recording for each participant takes 20–30 min.

We will record the participants' EEG data using a 19‐channel EEG system with passive electrodes (Science Beam; Parto Danesh Co., Iran). It has 19 scalp channels, a sampling rate of 500 Hz per channel, an ADC resolution of 24 bits, and a CMRR of 75 dB at 500 Hz. The electrode placement will follow the 10–20 international norm and referential montage linked ears. Every subject had a 5‐minute resting‐state EEG recording with their eyes open, followed by a 5‐min recording with their eyes closed, all while maintaining an impedance of less than 10 kΩ and applying a 0.5 low‐cut and a 500‐Hz high‐cut filter.

Finally, after the automated algorithm, manual checking by an expert neuroscientist for the artifact rejection process. Topographic maps will be generated for each QEEG feature in the frequency domain (e.g., absolute power, relative power, power ratio, peak frequency, amplitude asymmetry, coherence, and phase lag) for both responder and non‐responder groups using Neuro Guide software version 3.2.1.1 (Loo et al. 2016; Coburn et al. 2006).

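### Phase lag is credited with excluding volume conduction, but the quantity defined is a raw phase angle on a linked-ear reference, which zero-lag mixing and the shared ear signal bias towards 0

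*Protocol article*

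**What the plan says.** Section 1.2.2 (EEG Recording) lists seven families of QEEG parameter. For one of them it states: "Phase lag: A method for estimating connectivity in EEG in a way that excludes volume conduction effects". The sentences that follow describe something simpler. They present the measure as an ordinary angle with angular units, and sum it up so: "the phase difference between two waves is the difference between two waveforms relative to a common axis". No index that discards zero-lag interaction is named.

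The same section fixes the reference. Before the NeuroGuide software extracts the parameters, "the assembly of all the recorded data is defined based on the linked‐ear assembly", and the recording set-up is again given as "referential montage linked ears" on 19 scalp channels. No re-reference, Laplacian or reference-sensitivity analysis is described.

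Section 1.7.2 (Secondary Endpoint) includes coherence and phase lag among the features mapped in responders and non-responders and tested between the groups. ROC analysis of the QEEG biomarkers follows.

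**The concern.** Freedom from volume conduction belongs to measures that ignore the zero-lag part of an interaction, such as the phase lag index or imaginary coherence. A plain phase angle uses the whole cross-spectrum, including the part that instantaneous mixing and a common reference contribute. Section 1.2.2 therefore attaches the property of one kind of measure to the definition of another.

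What is at stake is interpretation. If phase or coherence separates responders from non-responders, the sentence tells the reader that field spread has already been ruled out, when on the stated definition it has not. The pilot is meant to supply effect sizes and candidate features for later trials, so a wrongly described feature could be carried forward under the wrong name.

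**Working it through.** The protocol gives no figure on this point, so there is none to reproduce. The check is whether the quantity it defines has the property it states.

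**Inputs from the protocol (1.2.2):** the measure is an angle between two waveforms; all data are on linked ears.

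**Assumptions (not in the protocol):** narrow-band signals with unit source amplitude; coupling c and true lag φ between two sources; zero-lag mixing m of each source into the other channel, with the same sign; an ear-reference signal of amplitude r, independent of the sources. Values tried: m from 0 to 0.5, r from 0 to 1.0.

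**Model.** With channels x = s1 + m·s2 − ref and y = s2 + m·s1 − ref, the cross-spectrum is

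S = c·e^(iφ) + 2m + m²·c·e^(−iφ) + r²

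The terms 2m and r² are real and positive, so they pull the angle of S towards 0.

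**Phase angle, true lag 60 degrees, c = 0.7**

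| m | r | Angle read (degrees) |
|---|---|---|
| 0 | 0 | 60.0 |
| 0.1 | 0 | 47.3 |
| 0.2 | 0 | 37.3 |
| 0.3 | 0 | 29.3 |
| 0.5 | 0 | 17.6 |
| 0 | 0.5 | 45.3 |
| 0 | 1.0 | 24.2 |
| 0.3 | 0.5 | 24.1 |
| 0.3 | 1.0 | 15.6 |

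Worked line for m = 0, r = 1.0: real part 0.7 × 0.5 + 1 = 1.35; imaginary part 0.7 × 0.866 = 0.606; atan(0.606/1.35) = 24.2 degrees. A simulation of 200,000 draws agreed with the closed form.

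**Second parameterisation.** With a shared zero-lag variance v only, coupling 0.3 and a true 90-degree lag, the angle is atan(0.3/v): 50, 31 and 17 degrees for v = 0.25, 0.5 and 1.0.

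**No true coupling (c = 0).**
- S is real, so its angle is 0 and no false non-zero mean lag appears.
- The mean absolute phase difference falls from 90 degrees to 78 or 60 from the reference alone (r = 0.5, 1.0), and to 57 from mixing alone (m = 0.3).
- Coherence magnitude from the reference is v/(1+v): 0.20, 0.33 and 0.50 for v = 0.25, 0.5 and 1.0. Squared coherence is 0.50² = 0.25 at r = 1.0 (v = r²), and 0.30 from mixing alone at m = 0.3.

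**What this does to a group comparison.**
- Equal reference in both groups (r = 1.0, m = 0, c = 0.7): a true lag of 60 degrees against a true lag of 0 is read as 24.2 against 0. The contrast shrinks.
- Identical true lag of 60 degrees, but r = 0.5 in one group and 1.0 in the other: 45.3 − 24.2 = about 21 degrees of difference with no neural difference.

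**Would a zero-lag-insensitive index cure it?**
- With no coupling, the phase lag index stayed at or below 0.005 for every m and r tried, so neither source created false connectivity.
- At c = 0.7 and 60 degrees, mixing alone left it unchanged (0.645 to 0.650).
- An active reference still shrank it: 0.645 to 0.552 at r = 0.5 and 0.409 at r = 1.0.
- Imaginary coherence behaves likewise: 0.606/(1 + r²) = 0.606, 0.485 and 0.303 for r = 0, 0.5 and 1.0.

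Such an index guards against false coupling but does not remove the effect of the reference on its size.

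**The case against.** The sentences after the claim may be a generic explanation of phase rather than an estimator, and the NeuroGuide algorithm is not shown. This stands as a limit on what can be said about the values that will be analysed. It does not rescue the text. If the software yields an angle, the claimed property is wrong; if it yields a zero-lag-rejecting index, the definition is wrong.

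A milder reading is that volume conduction alone cannot produce a non-zero lag. In the model that is true of the mean phase. Mixing still changes the size of a real lag, so the effect is not excluded from the measure.

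A reader might infer more than the protocol supports:

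- That a responder difference in phase or coherence would be a reference artefact. This needs mixing or ear signal to differ between groups. The protocol gives no reason to expect that: montage, impedance limit and time of day are common to all, and the EEG precedes treatment and responder classification.
- That the false-coupling figures contradict the quoted claim. They concern coherence, for which the protocol claims no such immunity.
- That most candidate features are affected. That assumes all 19 × 18/2 = 171 channel pairs are tested in each band, which section 1.7.2 does not say. What is certain is two of seven feature families.

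Finally, the aim is prediction, and a reproducible linked-ear feature may predict response whatever its source. That stands, and it is why these features need not be dropped.

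**Conclusion.** Section 1.2.2 states a property that the quantity it defines does not have, and the wording needs correcting whichever algorithm the software uses. The direction of the phase bias, towards 0, follows from the algebra for same-sign mixing and an independent reference signal. The size rests on mixing and reference levels that the protocol does not give; over the range tried, a true 60-degree lag reads as anything from 47 to 16 degrees.

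The expected consequence is bias and lost contrast in the phase measure, plus coherence that can be raised where there is no coupling. A spurious group difference is a conditional possibility, not a prediction. The primary endpoint, the proportion of responders, is untouched. The affected features belong to a secondary endpoint that the protocol itself presents as exploratory. The point is worth acting on because correction is cheap and changes what a positive phase or coherence result may be said to mean.

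**What to change.** In section 1.2.2, delete the claim of freedom from volume conduction for the phase-difference measure and name the estimator that the software computes.

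Add one zero-lag-insensitive index, named in advance (for example debiased weighted phase lag index or imaginary coherence), computed offline from the same recordings. Pair it with a re-referenced sensitivity analysis covering both that index and coherence, since the index alone still varies with the reference. Which alternative reference to use is a matter of judgement and no single choice is a clean test; it should be fixed before the groups are compared.

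State that linked-ear coherence and phase differences will not be interpreted as neural connectivity unless these analyses support it. They can still be reported as candidate predictors.

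The cost is data export, possibly a second software package, and a few more exploratory features in a 25-person pilot. No new recordings, visits or participants are needed.

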### Intervention

1.3

#### rTMS

1.3.1

TMS is a non‐invasive method that uses electromagnetic induction to stimulate the brain. By utilizing an insulated coil, TMS can depolarize or hyperpolarize neurons depending on the frequency of the applied stimulation. The magnetic pulses generated by the coil painlessly penetrate the scalp, bones, and brain membranes to reach the neurons, resulting in short‐term activity within the corresponding areas. Rapid and sequential delivery of these pulses, known as repetitive TMS, can induce longer‐lasting changes in brain activity (Sandrini et al. 2011). Furthermore, the pulse penetrates approximately 2.5 cm below the coil, affecting neurons in distant regions through synapses (Sharbafshaaer et al. 2024; Paganin and Contini 2025). In this treatment method, several key parameters are established, including the following: the stimulation site in the brain, the duration of stimulation, the interval between sessions, the total number of sessions, the number of pulses in each session, the pulse frequency, and the intensity (Chou et al. 2020; Zhang et al. 2021; Šimko et al. 2022). We will use the Magstim Rapid2‐Biphasic Stimulator (Magstim, Whitland, UK) equipped with the Double 70 mm Air Film Coil (AFC). We will first explain to participants the common and rare, but serious, side effects of rTMS and ask them to sign a consent form. Common side effects may include headaches (30%), facial muscle twitching (30%), lightheadedness or dizziness after treatment (20%), discomfort or pain at the stimulation site (20%), and fatigue (1%–7%). These side effects are usually mild, typically resolve during treatment, and can be alleviated by resting or taking over‐the‐counter pain medication such as ibuprofen or acetaminophen. Another possible side effect that occurs very rarely is an epileptic seizure (less than 0.1%) (Taylor et al. 2021). We will record all side effects reported by participants during the study. All procedures will be conducted between 4:00 p.m. and 8:00 p.m., as hormone levels related to the circadian cycle, such as melatonin and cortisol, can influence brain plasticity. Research indicates that the effectiveness of repetitive transcranial magnetic stimulation (rTMS) is higher when administered in the afternoon compared to the morning (Abo and Kakuda 2015). In the initial phase, it is imperative to ascertain the resting motor threshold (RMT), which will be evaluated based on the minimal intensity of stimulation applied to the primary motor cortex necessary to elicit a reliable motor‐evoked potential (MEP) in the first dorsal interosseous (FDI) muscle over five successive single pulses. It is important to set this threshold for each participant individually (Rossini et al. 2015) using established methods (Schutter and van Honk 2006). During each treatment session, the patient sits in a specially designed chair, similar to a dental unit. Before starting the treatment, the patient must remove all objects that are sensitive to magnetism, such as credit cards and jewelry around the head and neck, because a magnetic field will be created. Additionally, if possible, the patient will be given hearing protectors (in‐ear pads) to prevent any potential harm from the sound of the pulses.

The rTMS intervention will be initiated 2 weeks after the EEG recording. On the first day, we will mark the stimulation site, specifically the left DLPFC, on the scalp using the 5.5 cm method. Another approach for localizing the left DLPFC is called the Beam F3 method. Many studies have declared that the effectiveness and reliability of these two methods in targeting the DLPFC are comparable (Pace et al. 2023; Trapp et al. 2023). We will conduct a total of 10 treatment sessions, with 1 session per day for 5 consecutive days over 2 weeks. Each session will involve delivering 2000 pulses at a frequency of 20 Hz, with a cycle of 2 s on and 28 s off, lasting a total of 25 min. We will target 100% RMT. These parameters were selected based on a recent review suggesting that they can produce the optimal clinical outcome (Lefaucheur et al. 2014). Trained PhD students in neuroscience will continuously monitor rTMS sessions, including pulse rate, respiratory rate, and any adverse events.

We target the DLPFC because it is a key region for higher‐level cognition, and its pathological damage leads to a characteristic feature of MCI (Yan et al. 2023; Xie et al. 2021). Moreover, it plays a crucial role in some major brain networks, such as the central executive network (CEN) and the fronto‐parietal network (FPN), indicating that the left DLPFC is the most effective site to improve global cognition outcomes (Opitz et al. 2016; Agosta et al. 2012).

The SimNIBS‐3.2 toolbox was applied to investigate the efficacy of the electric field produced by rTMS through the left DLPFC under our protocol (Figure 2) (Thielscher et al. 2015).

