#### Eligibility Criteria

1.1.2

Inclusion criteria: (1) Persian language. (2) have the ability to visit the hospital. (3) all patients aged 60 years or older. (4) participants will be diagnosed with MCI in the Diagnostic and Statistical Manual of Mental Disorders‐5th edition (DSM‐V) and will be additionally assessed by the Montreal Cognitive Assessment (MoCA) (Badrkhahan et al. 2020) and the Mini‐Mental State Examination (MMSE) (Seyedian et al. 2008; Delbari et al. 2024) “22<MoCA<26 or 20<MMSE<24.” (5) not using of psychiatric or neurological medications. (6) patients who will sign informed consent forms.

Exclusion criteria: (1) a history of severe psychiatric problems such as a major depressive disorder or psychosis. (2) history of any neurostimulation treatments during the past 3 months. (3) contraindications to rTMS intervention, such as the presence of a cardiac pacemaker and ferromagnetic implants in the head or neck. (4) history of serious neurological illnesses, including epilepsy, seizures, or stroke. (5) abusing drugs or alcohol excessively. (6) with a skull fracture or craniotomy.

Patients diagnosed with MCI will be invited for EEG recording the next day. After EEG recording, those who consent to rTMS intervention will complete a screening questionnaire, supervised by a psychiatrist, prior to the treatment. The participants will all be eligible for TMS operation (Rossi et al. 2009; Mokhtarinejad et al. 2024) based on their responses to a TMS safety screening questionnaire. The TMS Safety Screening Questionnaire will be used to evaluate the eligibility for TMS intervention based on the questionnaire from Rossi et al. (2021), covering questions about the existence of risk factors, such as epilepsy or the presence of a cardiac pacemaker and ferromagnetic implants in the head or neck. According to their responses, patients will be categorized as either “Eligible,” or “Not eligible.”

Then complete an Iranian version of the 28‐item General Health Questionnaire (GHQ) (Ebrahimi et al. 2007). The General Health Questionnaire (GHQ‐28) is a general health screening tool, and obtaining a score of 24 (Ebrahimi et al. 2007) or higher is a condition for volunteers to continue participating in the study, as well as not having any TMS contraindications.

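### Hearing protection during rTMS is conditional, so the text allows a participant to be stimulated without it

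*Protocol article*

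**What the plan says.** Section 1.3.1 (rTMS) describes the preparation for each treatment session and sets two precautions in consecutive sentences. The first is unconditional: "the patient must remove all objects that are sensitive to magnetism". The second is qualified: "if possible, the patient will be given hearing protectors", in the form of in-ear pads, with the stated aim "to prevent any potential harm from the sound of the pulses".

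The same section fixes the dose. On pulses it says: "Each session will involve delivering 2000 pulses at a frequency of 20 Hz". The timing within a session is given as follows: "with a cycle of 2 s on and 28 s off, lasting a total of 25 min". On the number of sessions it says: "We will conduct a total of 10 treatment sessions". Trained staff "will continuously monitor rTMS sessions, including pulse rate, respiratory rate, and any adverse events", and the side effects that participants report are recorded.

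Section 1.1.2 (Eligibility Criteria) describes the TMS safety questionnaire as "covering questions about the existence of risk factors, such as epilepsy or the presence of a cardiac pacemaker"; metal implants near the stimulation site are the remaining example.

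**The concern.** The protocol itself treats pulse noise as a potential source of harm and ear protection as the preventive measure, so the point needs no outside guideline. Providing pads is the default, but the qualifier opens an exception that is not defined, and stimulation may proceed within it.

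The qualifier can be read in two ways. If it means that the participant can tolerate the pads, someone who cannot wear them may be treated unprotected. If it means that pads are available, anyone could be affected on a day without supply. Neither case would be a protocol deviation, so neither would have to be recorded as one.

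What is at stake is participant safety. The responder proportion, the QEEG comparison and their analysis do not depend on it.

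**Working it through.** No figure in the plan is in dispute. The check compares the relevant provisions and then works out how much stimulation the exception would cover.

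**Provisions compared**

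| Provision | Where | Does it make ear protection compulsory? |
|---|---|---|
| Removal of magnetically sensitive objects | 1.3.1 | No, but it is itself worded as compulsory |
| In-ear pads | 1.3.1 | No, the provision is conditional |
| Session monitoring (pulse rate, respiratory rate, adverse events) | 1.3.1 | No, it detects harm but does not prevent it |
| Recording of reported side effects | 1.3.1 | No, for the same reason |
| TMS safety questionnaire and rTMS contraindications | 1.1.2 | No, these select participants and do not protect them during a session |

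The questionnaire and the contraindication criterion both give their contents as examples, so the article does not show whether hearing is asked about. The point does not rest on this: even a question about hearing would not oblige staff to protect the ears.

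**Stimulation covered by the exception**

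Inputs, all from section 1.3.1: 2000 pulses per session, 20 Hz, 2 s on and 28 s off, 25 min per session, 10 sessions.

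1. Pulses per train: 20 Hz × 2 s = 40.
2. Trains per session: 2000 / 40 = 50.
3. Session length: 50 × (2 + 28) s = 1500 s = 25 min. This reproduces the protocol's own figure, so the dose parameters are consistent.
4. Pulse delivery per session: 50 × 2 s = 100 s, and 100 / 1500 = 6.7% of session time. The rest is off time.
5. Full course: 10 × 2000 = 20,000 pulses, and 10 × 100 s = 1,000 s of pulse delivery.

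Pulses used to find the resting motor threshold come on top. The article does not give their total number.

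These figures describe exposure, not harm. The article states no sound level and no number of participants for whom protection might not be possible.

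**The case against.** The strongest reply is that the measure is already planned. The device, the default and the purpose are all stated, and the qualifier may be loose drafting or a sensible allowance for someone who cannot tolerate in-ear pads. The document is also a condensed journal article. Who judges feasibility, what alternative is used and when a session is withheld are operating details that a fuller protocol may contain. Taking off metal objects is always within the patient's control, whereas wearing pads depends on fit and tolerance, so different wording for the two precautions is not a contradiction. Finally, no harm is demonstrated, and a hearing complaint would be picked up by the monitoring and the side-effect record.

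Much of this stands. The words may well be loose drafting, the text does not show that anyone will be treated unprotected, and the two sentences do not contradict each other. The missing operating details are no fault in themselves.

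What the reply does not remove is the condition. The article is not silent on hearing protection: it states a rule, and that rule, followed exactly, allows unprotected stimulation. A stricter operating manual would differ from the published text. Monitoring and side-effect recording act after the event.

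**Conclusion.** The concern holds, as a minor participant-safety point. Per affected participant, the wording permits up to 10 unprotected sessions, that is 20,000 treatment pulses and about 1,000 s of pulse delivery, without a deviation. The number affected is unknown and may be zero, and no hearing risk is estimated.

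The conclusion rests on reading the qualifier as written and on the article containing no other provision that makes protection compulsory. It assumes nothing about how loud the device is.

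**What to change.** Delete *if possible* and require hearing protection for every participant at every rTMS session. Add one sentence: where in-ear pads cannot be worn, alternative protection is used or stimulation is withheld, and the decision is documented. It would be sensible to apply the same rule while the motor threshold is being determined.

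The cost is two words removed and one sentence added. In-ear pads are already foreseen, so the only extra supply is alternative protection for someone who cannot wear them, for up to 10 sessions. The downside is that a participant who can wear no protection at all would not be treated. Each such case would remove 1/25 = 4% of the planned sample; this is the cost of one case, not an expected frequency, and it should be rare.
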